### Randomization and blinding

2.4

The allocation to placebo control or YKSCH treatment group of subjects meeting the eligibility criteria will be performed by an independent statistician via computer-generated block randomization. For assessing secondary outcomes, PSG and hormone analysis will be performed for some of the subjects from the treatment and control groups at a 1:1 ratio; the subjects will be selected by an independent statistician, using systematic sampling. Each subject will receive an identification code enclosed in an opaque envelope. The identification code shall indicate whether PSG and hormone analysis will be performed. The subjects, researchers, and assessors collecting the data will be blind to group assignment, as this study is designed to be double blind. If unblinding is required, such as occurrence of medical emergency, the principal investigator decides to remove the blindness through the researchers’ meeting. In this case, the institutional review board (IRB) should be informed of the unblinding and explain the medical emergency in detail within 24 hours enrollment of subjects, allocation sequence, and assignment of subjects will be the responsibility of the Clinical Trial Center at Dunsan Korean Medical Hospital of Daejeon University.

### Interventions

2.5

Both groups will receive conventional anti-PD medicines, including L-DOPA, dopamine agonists, catechol-*O*-methyl transferase (COMT) inhibitor, and monoamine oxidase (MAO) inhibitor, and will be prohibited from undergoing herbal medicine treatment. We will perform all examinations and assessments in the dopaminergic “on” state (the same time in each patient, after administering the last dose of conventional medication). A constant dose of conventional medication will be maintained during treatment and the follow-up period. If receiving neuropsychiatric drugs, such as sedatives, hypnotics, anxiolytics, selective serotonin uptake inhibitor, and sleep stabilizers, a stable dose of these drugs will have to have been maintained for at least 1 month prior to enrollment. Both YKSCH and placebo drugs will be packed in opaque sachets in granular form to blind researchers and subjects, and will be administered orally 3 times daily. Criteria for discontinuing allocated interventions for subjects are: withdrawal of the clinical trial participation agreement by subjects or their legal representatives, violation of the selection/exclusion criteria during clinical trial, occurrence of adverse events, and less than 70% compliance with medication criteria. To improve adherence to interventions, the *clinical research coordinator will assess medication criteria adherence (number of medicines received/number of medicines to be received)* every time the subjects visit the clinic.

#### Treatment group: YKSCH

2.5.1

Nine dried medicinal herbs constitute YKSCH: *Atractylodis rhizoma*, *Poria sclerotium*, *Cnidium rhizome*, *Uncaria* sp. hook, Japanese Angelica root, *Bupleurum* sp. root, *Glycyrrhiza* sp., *Citrus* sp., and *Pinellia ternata*. The treatment group will receive YKSCH. The formula will be supplied by the manufacturer Kyungjin Pharmaceutical Co., Ltd. (Icheon, Republic of Korea), and be manufactured in compliance with Good Manufacturing Practice under Ministry of Food and Drug Safety guidelines. The final form of YKSCH is granular.

#### Control group: placebo

2.5.2

The control group will be administered the placebo drug. The placebo drug will be manufactured using the same process as YKSCH, by the same manufacturer; it will be made of lactose, starch, and caramel coloring.

### Outcome measures

2.6

Any outcome assessments without PSG and hormone analysis will be performed in the dopaminergic “on” state at the same time for each subject, after administering the last dose of conventional anti-PD medicine.

The schedule for outcome measurements is presented in Figure 1.

**Figure 1 F1:**
[figure not shown]
Schedule of YKSCH or placebo treatment and collection of outcome measurements. The treatment or control groups will be administered YKSCH or placebo drug, respectively. The subjects will receive YKSCH or placebo for 12 weeks, and be followed-up for 4 weeks. Administration of SCOPA-S, to assess primary outcome; PSG; collection of blood samples for analysis of NT and hormone levels; fNIRS measurement will be performed at 0 and 12 weeks (indicated by black arrows). Questionnaire surveys related to sleep disturbance will be conducted at 0, 4, 8, 12, and 16 weeks (indicated by black and hollow arrows). fNIRS = functional near-infrared spectroscopy, NT = neurotransmitter, PSG = polysomnography, SCOPA-S = Scales for Outcomes in PD-Sleep Scale, YKSCH = Yokukansankachimpihange.

#### Primary outcomes

2.6.1

##### Scales for outcomes in PD-sleep scale

2.6.1.1

The score of SCOPA-S, which is a questionnaire survey assessing problems in both night- and day-time sleep, and the measurement of PD^[4,9,21]^ the severity will be the primary outcomes measured in this study. The survey will be conducted at baseline (visit 1) and 12 weeks after treatment (visit 4) for both groups.

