#### Instruments to assess sleep disturbance in PD

2.6.3

Parkinson's Disease Sleep Scale (PDSS), Epworth Sleep Scale (ESS), NPI, Beck Depression Inventory (BDI), and Perceived Stress Scale (PSS) scores will be assessed at visits 1–5 for both groups. The PDSS and ESS are valid tools for evaluating sleep disturbance in PD^[22]^ and measuring day-time sleepiness,^[23]^ respectively. For assessing several symptoms related to sleep disturbance, NPI,^[24]^ BDI,^[6]^ and PSS^[25]^ scores will be assessed as secondary outcomes. The NPI is considered a valid instrument to evaluate behavioral and psychological symptoms, including sleep disorder.^[24]^ The BDI will be used to assess depression, one of the leading causes of insomnia.^[6]^ Stress is also known to be associated with sleep quality, and the PSS assesses subjective appraisals of stressful situations.^[25]^

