### Safety assessment and adverse events

2.8

Safety assessment for all subjects will be performed via clinical laboratory examination at baseline, before drug administration; 4 weeks after drug administration (visit 2); and 12 weeks, after completing drug administrations (visit 4). Laboratory tests will include those for live rand renal function, which can possibly be damaged by herbal medicines,^[2]^ and serum potassium concentration because *Glycyrrhiza radix*, a component of YKSCH, can induce hypokalemia.^[3]^ Adverse events will be defined as undesirable and/or unexpected medical findings which did not occur before the start of this clinical trial, and will be recorded, regardless of their relation to YKSCH or the placebo drug. The severity of the adverse events will be evaluated based on the step-wise criteria established by the chief investigator, and reported to the IRB of Daejeon University. Following appropriate deliberation, the IRB will determine whether the trial should be discontinued. Causal link between the adverse events and the procedure will be investigated by the doctor-in-charge, and categorized into 6 stages based on the aforementioned evaluation criteria. In case of a severe adverse event, appropriate treatment and follow-up will be provided.

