#### Statistical analysis

2.9.2

Statistical and fNIRS data analyses will be performed by statisticians and a researcher from a different group. An intention-to-treat analysis will be performed in case of subjects lost to follow-up, and multiple imputations will be applied for the missing data. Statistical analysis will be performed using SPSS software for Windows, version 24.0, (Chicago, IL). The SCOPA-S score, which is the primary outcome, will be evaluated by calculating the difference between the mean scores before and after receiving YKSCH or placebo (for treatment or control groups, respectively). Independent two-sample *t*-test (or the Mann–Whitney *U* test for nonparametric samples) will then be performed to analyze the difference between the treatment and control groups. The results of the questionnaire survey, including PDSS, ESS, NPI, BDI, and PSS, scored at 0, 4, 8, and 12 weeks, respectively, and NT levels measured at 0 and 12 weeks will be analyzed using independent two-sample t-tests (or the Mann–Whitney *U* test for non-parametric samples). To compare sleep metrics obtained using PSG and measurement of hormone levels, pre- and post-YKSCH or placebo treatment at weeks 0 and 12, paired t-tests (or the Wilcoxon signed-rank test) will be used. The mean oxyhemoglobin and deoxyhemoglobin concentrations determined using fNIRS at 0 and 12 weeks will be analyzed using repeated-measures analysis of variance. Pearson's correlation coefficient will be used to assess the association among subscales of the questionnaire surveys, oxyhemoglobin and deoxyhemoglobin concentrations, and NT levels. The level of statistical significance will be set at *P < *.05, and 95% confidence intervals will be calculated. A statistician will be consulted incase the obtained data need to be calibrated.

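### The primary SCOPA-S score is taken only at weeks 0 and 12, though other questionnaires are filled in at weeks 4 and 8, so subjects who leave before week 12 give the imputation no post-baseline primary value

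*Protocol article*

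**What the plan says.** The section on the SCOPA-S (2.6.1.1) fixes the primary outcome at two time points: "The survey will be conducted at baseline (visit 1) and 12 weeks after treatment (visit 4) for both groups". The safety section (2.8) places visit 4 at "12 weeks, after completing drug administrations (visit 4"), so it is the end of treatment. The Figure 1 legend agrees, listing SCOPA-S among the assessments made at weeks 0 and 12 only.

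Section 2.6.3 treats PDSS, ESS, NPI, BDI and PSS differently: "scores will be assessed at visits 1–5 for both groups". The Figure 1 legend gives the weeks: "Questionnaire surveys related to sleep disturbance will be conducted at 0, 4, 8, 12, and 16 weeks".

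On missing data, section 2.9.2 says: "An intention-to-treat analysis will be performed in case of subjects lost to follow-up, and multiple imputations will be applied for the missing data". The primary comparison is a two-sample test on the before-after change in SCOPA-S. Section 2.9.1 allows for 10% dropout in a total of 34. Besides withdrawal of consent, section 2.5 gives as reasons for discontinuing the allocated intervention: "violation of the selection/exclusion criteria during clinical trial, occurrence of adverse events, and less than 70% compliance with medication criteria". It does not say whether such subjects still attend visit 4.

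**The concern.** SCOPA-S is the one questionnaire left out of visits 2 and 3, which take place anyway. For a subject who leaves before week 12, the trial will hold a baseline primary score and nothing later on that scale. An imputation model can then learn about that subject's course only from baseline SCOPA-S or from other instruments. If leaving depends on how the subject was doing, and does so differently in the two arms, the imputed values will be systematically off and the treatment difference will be biased. Adverse events and poor compliance are reasons for stopping that could plausibly differ by arm.

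The schedule has to be settled before recruitment. An analysis plan can choose an imputation model, but it cannot supply SCOPA-S values that were never collected.

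**Working it through.** **How many subjects.** Expected number without week 12: 34 × 0.10 = 3.4. Chance of at least one: 1 − 0.9^34 = 0.97. If leaving is spread evenly over 12 weeks (assumed), two thirds leave after week 4. Collecting SCOPA-S at weeks 4 and 8 would then give 3.4 × 2/3 = 2.3 of them at least one post-baseline value and leave 1.1 with none.

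**The plan's own figure.** The effect size behind 34 is not printed, so the sample size cannot be reproduced forward. Working back: 15 / 0.9 = 16.7, rounded up to 17 per arm, so 15 evaluable per arm. Power of 80% at two-sided 5% with 15 per arm needs a standardised effect of 1.06 (noncentral t). I use this for power below.

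**Bias if imputation uses baseline SCOPA-S only.** The article gives no correlations, so all of these are assumptions:
- true week-12 difference 1.0 SD, normal scores;
- on placebo, the share p with the worst week-8 score stops; on active, a random share p stops;
- correlation r between post-baseline visits, 0.6 to 0.8;
- correlation b of baseline with later visits, from 0.5 up to r;
- regression imputation within arm.

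Let z be the upper p point of the standard normal, φ(z) its density, λ = φ(z)/(1 − p) and k = λ(λ + z). Placebo stayers have a week-12 mean rλ too favourable and a baseline mean bλ too favourable. Among stayers the slope of week 12 on baseline is s = b(1 − rk)/(1 − b²k). Imputation gives back s·b·λ, so the effect is understated by λ(r − b·s).

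- p = 0.10: z = 1.2816, λ = 0.1755/0.9 = 0.195, k = 0.288.
- p = 0.20: z = 0.8416, λ = 0.2800/0.8 = 0.350, k = 0.417.

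Example with p = 0.20, r = 0.8, b = 0.5: s = 0.5 × (1 − 0.8 × 0.417)/(1 − 0.25 × 0.417) = 0.372; understatement = 0.350 × (0.8 − 0.5 × 0.372) = 0.215 SD.

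| r | b | 10% stopping | 20% stopping |
|---|---|---|---|
| 0.6 | 0.5 | 7.4% | 13.7% |
| 0.8 | 0.5 | 11.6% | 21.5% |
| 0.6 | 0.6 | 5.2% | 9.9% |
| 0.8 | 0.8 | 3.8% | 7.6% |

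A simulation with 400,000 per arm gives the same values.

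**With auxiliaries.** In the same simulation I added a PDSS-like scale at weeks 4 and 8, with an assumed correlation of 0.6 with the SCOPA-S score of the same visit. The understatement falls to about 3–7% at 10% stopping and 6–14% at 20%. Adding SCOPA-S itself at weeks 4 and 8 takes it to zero, but that is partly by construction, because stopping here is driven by the week-8 SCOPA-S score.

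**Same mechanism in both arms.** Both arm means shift by the same amount and the difference is essentially unbiased.

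**Power.** Taking effective n per arm as observed + missing × r², with r from 0.3 to 0.8 for the correlation of the intermediate measure with week-12 SCOPA-S:
- 10% missing: 15.3 observed; effective n 15.45 to 16.39; power 81–84%, against 81% with completers only.
- 20% missing: 13.6 observed; effective n 13.91 to 15.78; power 77–82%, against 76%.

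**The case against.** The strongest reply is that nothing here is an error. Baseline and end of treatment are a legitimate pair of time points for a small pilot, the sections agree on them, and the planned test uses exactly that change. This stands.

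The second reply is that imputation need not use baseline SCOPA-S alone. Section 2.9.2 does not restrict the model, model details belong in an analysis plan, and PDSS and ESS at weeks 4 and 8 cover the night-time and daytime aspects that SCOPA-S measures. This stands in part: under the assumptions above, such auxiliaries remove some of the bias, but a different scale replaces the primary scale only incompletely.

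Third, the size depends on a constructed case in which stopping is response-driven in one arm and random in the other. Even the largest value at the planned dropout, about 0.12 SD, is small beside a standard error of √(2/15) = 0.37 SD at 15 per arm. That also stands.

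Stronger readings are tempting, and the document does not support them:
- A reader might infer that everyone who stops study drug lacks a primary value. Section 2.5 concerns stopping the intervention; a subject who stops and still attends visit 4 has one.
- A reader might infer that intention-to-treat is nominal because it is mentioned next to loss to follow-up. One condensed sentence cannot carry that.
- A reader might blame the schedule for the loss of power as numbers shrink (80% at 15 per arm, 70% at 12, 61% at 10). That is the cost of losing subjects.
- A reader might count the missing week-16 SCOPA-S as part of the problem. A value after the end of treatment does nothing for someone who left before week 12.

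**Conclusion.** The point holds as an avoidable weakness of modest size. Subjects who leave before week 12, about 3 to 4 of 34 at the planned dropout, will have no post-baseline SCOPA-S value, and no later analysis plan can restore it. If dropout is response-driven on placebo only and imputation uses baseline alone, the effect is understated by about 4–12% at 10% stopping and 8–21.5% at 20%, less with good auxiliaries. By symmetry, the mirror pattern would overstate it by the same amount; the same mechanism in both arms would leave it nearly unbiased. These figures rest on assumed correlations and an assumed dropout mechanism, not on anything the article reports. The gain in power at 10% dropout is small. The case for acting is that the remedy costs very little and protects the primary comparison if dropout turns out higher or more selective than planned.

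**What to change.** Add SCOPA-S to the existing questionnaire pack at visits 2 and 3 (weeks 4 and 8). Use these values, with the PDSS and ESS scores, in the imputation model; or analyse weeks 4, 8 and 12 in a mixed model with the week-12 contrast as primary. State that subjects who stop study drug are still assessed at visit 4 and are analysed in the arm to which they were randomised. A week-16 SCOPA-S is optional: it would show persistence but does not address early dropout.

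The cost is a few more minutes at two visits that already take place, changes to protocol, case report form and registry wording, and some effort to retain subjects who are off drug. The sample size stays at 34, no visit is added, and the criteria for stopping the intervention are untouched.

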#### Secondary outcomes

2.6.2

The secondary outcome measures include findings from 5 instruments evaluating sleep disorders, PSG and sleep-related hormone analysis, changes in the levels of NTs associated with PD, and hemodynamic changes in the PFC during verbal fluency task of subjects.

#### Instruments to assess sleep disturbance in PD

2.6.3

Parkinson's Disease Sleep Scale (PDSS), Epworth Sleep Scale (ESS), NPI, Beck Depression Inventory (BDI), and Perceived Stress Scale (PSS) scores will be assessed at visits 1–5 for both groups. The PDSS and ESS are valid tools for evaluating sleep disturbance in PD^[22]^ and measuring day-time sleepiness,^[23]^ respectively. For assessing several symptoms related to sleep disturbance, NPI,^[24]^ BDI,^[6]^ and PSS^[25]^ scores will be assessed as secondary outcomes. The NPI is considered a valid instrument to evaluate behavioral and psychological symptoms, including sleep disorder.^[24]^ The BDI will be used to assess depression, one of the leading causes of insomnia.^[6]^ Stress is also known to be associated with sleep quality, and the PSS assesses subjective appraisals of stressful situations.^[25]^

#### Polysomnography and hormone analysis

2.6.4

For objective sleep assessment, total recording time, sleep period, waking after sleep onset, total sleep time, sleep onset, sleep efficiency, number of awakenings, sleep latency to N1, sleep latency to N2, sleep latency to N3 (slow wave sleep), and stage R latency from sleep onset will be measured using PSG (Embletta MPR PG, Natus Medical Incorporated, Pleasanton, CA, USA). The subjects will be examined using in-laboratory PSG for one night. The PSG assessment will be set up and performed by a trained sleep technologist, using an Embletta MPR.^[26]^ This device consists of multiple channels for electroencephalography, electrocardiography, electrooculography, airflow, etc. Recordings from the electroencephalogram channels (C3-M2, C4-M1, O1-M2, O2-M1, F3-M2, and F4-M2) in the frontal, central, and occipital regions of the head, electrooculography channels (LOC-M2 and ROC-M1), and electromyography channel (EMG1-EMG2) in both legs will be acquired for each subject. Nasal and oral airflow, recorded using oral/nasal thermistor airflow and pressure nasal cannula, will be measured. In addition, oxygen saturation, using pulse oximetry; movements of the chest and abdomen; behavior during sleep, using video recording; change of body position, such as supine, left, right, prone, and upright, and snoring; and pulse rate will be recorded. Scoring of the sleep stages will be performed according to the American Academy of Sleep Medicine rules.^[27]^ Blood sampling, for measurement of cortisol and melatonin levels, will be conducted every 4 hours, over 24 hours, via venous catheter. Hormone levels will be examined using a melatonin enzyme-linked immunosorbent assay (ELISA) kit (ab213978; Abcam, Cambridge, MA) and a cortisol parameter assay kit (KGE008B, R&D systems, Minneapolis, MN).

#### Molecular analysis: plasma and serum levels of neurotransmitters

2.6.5

Investigation of changes in the plasma and serum NT levels may help us to understand the mechanism of action of YKSCH in patients with PD experiencing sleep disturbance. The serum levels of the PD-related NTs, dopamine, GABA, glutamate, norepinephrine, epinephrine, and serotonin, will be analyzed.^[28]^ Blood collected from the patients in both groups, at baseline (visit 1) and after treatment (visit 4), will be immediately centrifuged at a temperature below 4°C. The obtained plasma and serum samples will be stored at a temperature below −80°C until further analysis. The samples will be analyzed by Seoul Clinical Laboratories in South Korea, a quality facility certified by the European Quality Assurance Agency. The levels of dopamine, epinephrine, and norepinephrine will be measured using a high-performance liquid chromatography-electrochemical detection system (Agilent Technologies, Santa Clara, CA). The glutamate and GABA levels will be measured using ion-exchange chromatography (Biochrom Ltd., Cambourne, Cambridge, UK). The serotonin levels will be measured using the ELISA Fast Track kit (Labor Diagnostika Nord, Nordhorn, Germany). For hormone analysis, the subjects will be asked to abstain from drinking, smoking, and consumption of caffeine, turkey meat, bananas, and tomatoes, beginning the day before the test, as these can affect sleep rhythm and melatonin secretion.^[8]^ The night before hormone analysis, the subjects will be instructed to turn off the lights and attempt to sleep at 10 pm, and the use of electronic devices, such as smart phones and televisions, will be prohibited on the day before the evaluation.

#### Neuroimaging: functional near-infrared spectroscopy

2.6.6

The response in the frontal regions of the brain has previously been measured using fMRI during a verbal fluency task (VFT) in patients with chronic insomnia, and is known to be affected by sleep deprivation; in this study, decreased activation in the cortex was attenuated after effective treatment.^[29]^ Hemodynamic responses, measured using fNIRS, during a VFT showed hypoactivation in the PFC of patients with chronic insomnia.^[30]^ Therefore, our intention is to determine whether the concentrations of oxygenated hemoglobin in the PFC of patients with PD exhibiting sleep disorder is increased by YKSCH administration, using fNIRS during VFT. The test will be performed at baseline (visit 1) and after treatment (visit 4) in both groups. The subjects will perform a VFT in which they must speak as many items as possible within the given semantic categories. The measurements will be performed by an experienced user of the fNIRS system.

The noninvasive optical imaging, fNIRS system (NIR Scout 1624, NIRx Medical Technology, Berlin, Germany) is used to measure changes in the cerebral concentrations of oxyhemoglobin and deoxyhemoglobin.^[31]^ This system utilizes the transmission of near-infrared light at 2 wavelengths (760 and 850 nm), with a power of 5 mW per wavelength, and comprises 16 light-emitters and 16 photodetectors. The probes will be placed on the head of each subject, at a region corresponding to the PFC. Data collection and analysis will be performed using Nirs LAB version 201601 (NIRx Medizintechnik GmbH, Berlin, Germany).

Based on the difference in absorption spectra of the detected signal, assuming constant light scattering, changes in the concentrations of oxyhemoglobin and deoxyhemoglobin in the targeted PFC region will be measured using the modified Beer–Lambert law.^[32]^ The data for the measured oxyhemoglobin and deoxyhemoglobin concentrations will be exported to MATLAB (MATLAB and Statistics Toolbox Release 2012b, The Math Works, Inc., Natick, MA),^[32]^ calculating the mean oxyhemoglobin and deoxyhemoglobin concentrations for each patient.

